## Abstract

**Background:**

The global prevalence of type 2 diabetes is increasing. Effective strategies to address this public health challenge are currently lacking. A number of epidemiological studies have reported associations between low concentrations of 25-hydroxy vitamin D and the incidence of diabetes, but a causal link has not been established. We investigate the effect of vitamin D supplementation on the metabolic status of individuals at increased risk of developing type 2 diabetes.

**Methods/design:**

In a randomised double-blind placebo-controlled trial individuals identified as having a high risk of type 2 diabetes (non-diabetic hyperglycaemia or positive diabetes risk score) are randomised into one of three groups and given 4 doses of either placebo, or 100,000 IU Vitamin D_2_ (ergocalciferol) or 100,000 IU Vitamin D_3_ (cholecalciferol) at monthly intervals. The primary outcome measure is the change in glycated haemoglobin level between baseline and 4 months. Secondary outcome measures include blood pressure, lipid levels, apolipoproteins, highly sensitive C-reactive protein, parathyroid hormone (PTH) and safety of supplementation. and C-reactive protein. The trial is being conducted at two sites (London and Cambridge, U.K.) and a total of 342 participants are being recruited.

**Discussion:**

Trial data examining whether supplementation of vitamin D improves glycaemic status and other metabolic parameters in people at risk of developing type 2 diabetes are sparse. This trial will evaluate the causal role of vitamin D in hyperglycaemia and risk of type 2 diabetes. Specific features of this trial include recruitment of participants from different ethnic groups, investigation of the relative effectiveness and safety of vitamin D_2_ and D_3_ and an evidence based approach to determination of the dose of supplementation.

**Trial registration:**

EudraCT2009-011264-11; ISRCTN86515510

## Background

The number of people with diabetes is increasing across the world, with the latest estimates from the International Diabetes Federation predicting a rise from 366 million in 2011 to 552 million in 2030 [1]. The clinical consequences of type 2 diabetes (T2D) including macrovascular and microvascular disease, and related premature mortality [2] make it a condition of major public health importance. As such, the identification of risk factors for T2D, particularly those that might be potentially modifiable, is of great interest.

There is convincing evidence that changes to diet and physical activity can help to prevent or delay the onset of T2D among those at high risk [3-6]. However, intensive lifestyle modification interventions are difficult to sustain and costly to implement. Thus, there is interest in identifying complementary strategies that might help in the prevention of T2D. There is accumulating evidence that vitamin D insufficiency is associated with the risk of developing T2D [7-9]. Whether supplementation of vitamin D can delay or prevent T2D is unknown.

Epidemiological studies have examined the association between dietary vitamin D intake and the risk of diabetes [10,11], but these omitted information on the major non-dietary component of vitamin D from endogenous synthesis through sun exposure. Circulating 25-hydroxyvitamin D (25[OH]D) concentration is the best indicator of vitamin D status as it accounts for both vitamin D intake and endogenous synthesis [12]. More recent epidemiological studies have examined the association between circulating 25(OH)D concentrations and incident diabetes, and the findings have been largely consistent, demonstrating an inverse association. Such findings have been summarised in systematic reviews and meta-analyses [7-9], with the latest one from our group showing a 41% (95% confidence interval 33% to 48%) lower risk for those in the highest versus the lowest quartile of 25(OH)D [7]. Whilst meta-analysis deals with issues of consistency and precision, it does not resolve the problems of confounding and selection bias in observational studies. To address the question of whether observed associations between vitamin D and risk of T2D are causal in nature, there is a need to conduct randomised controlled trials of supplementation.

Two clinical trials that examined incident diabetes as an outcome found no effect of supplementation with 400 IU/day and 800 IU/day of vitamin D respectively [13,14]. In the larger of these trials (the Women’s Health Initiative randomised controlled trial), there was no association between vitamin D supplementation (in combination with calcium supplementation) and T2D incidence (hazard ratio 1.01, 95% CI: 0.94; 1.10) [13]. A causal link could not be ruled out by this trial, however, as it tested a low dose of 400 IU/day of vitamin D_3_[15]. In two separate systematic reviews, Mitri and Pittas et al. synthesised the available evidence on clinical trials of the effect of vitamin D supplementation on diabetes incidence (8 trials) or intermediate outcomes such as levels of glycaemia (11 trials) [8,9]. Overall, few were considered of good quality, but there was no overall benefit of supplementation with vitamin D. Of five trials measuring insulin resistance as an outcome [8], only one in New Zealand among vitamin D deficient (25(OH)D< 50 nmol/l) South Asian women reported significant improvement assessed by homeostasis model assessment [16]. More recently, Pittas’ group investigated whether vitamin D supplementation, with or without calcium, improved glucose homeostasis in adults at high risk of diabetes [17]. They included 92 adults (mean BMI 32 kg/m^2^, mean glycated haemoglobin of 5.9% (41 mmol/mol)) who were randomly assigned in a 2-by-2 factorial-design trial, to receive either cholecalciferol (2000 IU once daily) or calcium carbonate (400 mg twice daily) for 16 weeks. They reported improved beta cell function in the vitamin D supplemented group with increased glucose disposition index and improved insulin secretion. There was no significant effect on glycated haemoglobin (HbA_1c_) level, although there was a tendency toward greater attenuation in the rise in HbA_1c_ over follow up. There was also no significant effect of calcium supplementation. Two further trials have since been published showing no associations between supplementation with relatively high dose vitamin D and markers of insulin sensitivity [18,19]. These trials were restricted to minority groups (Latin Americans or African Americans) or women, and a common feature was the successful increase in 25(OH)D level following D_3_ supplementation. In the Davidson et al. study [18], there was also no effect on diabetes incidence, but follow up was short at 12 months. However, at 12 months, HbA_1c_ levels were significantly lower in the vitamin D group compared with the placebo group. Taken together, the evidence to date from trials is suggestive but not conclusive, and there is further need for well-designed trials, with adequate sample size, adequate dose of supplementation and good adherence, to advance this field of enquiry. Three particular issues are of further interest. The first relates to the dose of supplementation. Recent Institute of Medicine (IOM) guidelines suggested that the vitamin D needs of at least 97.5% of the population would be met by a recommended dietary allowance (RDA) of 600 IU/day for adults aged up to 70, and 800 IU/day after the age of 71 years [20]. IOM also raised the safe limit of vitamin D intake to 4000 IU/day and suggested that a serum concentration of 50 nmol/l is sufficient for most people [21]. However, several authors have suggested that IOM recommendations are focussed on bone health alone, do not account for potential extra-skeletal effects and are therefore too conservative [22]. A growing body of evidence suggests that larger doses than those previously investigated (equivalent to 2,000 IU – 10,000 IU daily) are required to optimise vitamin D status [15].

A second issue relates to whether vitamin D_2_ (ergocalciferol) or vitamin D_3_ (cholecalciferol) is likely to be more effective, or whether they would have equivalent effects on glycaemia. Previously thought to be equipotent in elevating serum 25(OH)D, several studies now suggest that vitamin D_2_ is less effective than vitamin D_3_[23-27]. In contrast, a trial by Hollis et al. reported that vitamin D_2_ and D_3_ were equivalent in their ability to maintain circulating levels of 25(OH)D over 11 weeks of supplementation [28]. Most recently, based on a meta-analysis of clinical trials that directly compared the 25(OH)D raising effects of supplementation with D_2_ or D_3_, Tripkovic et al. concluded that D_3_ supplementation is more efficacious [29]. However, according to the free hormone hypothesis, despite being less efficacious in elevating total 25(OH)D levels, 25(OH)D_2_ may be more available to exert biological activity being less tightly protein bound than 25(OH)D_3_. However, the effects of factors such as hydroxylation rates and deactivation of D_2_ and D_3_ on biological activity are unclear, and no trial has yet reported on the comparative effects of D_2_ and D_3_ on glycaemia.

A further issue relates to the effectiveness of vitamin D supplementation in people from different ethnic groups. Melanin in the skin reduces vitamin D production and hence the darker the skin pigmentation, the lower the synthesis of vitamin D for equivalent sun exposure [30]. In a study in the United States, researchers exposed healthy young individuals from different races to similar doses of UVB rays and measured the 25(OH)D concentrations before and after exposure. Baseline concentrations were similar, but Caucasians had highest concentrations of 25(OH)D following UVB exposure, followed by East Asians, South Asians and Blacks [31]. Concentrations of 25(OH)D in Hispanics and African-Americans are lower than those among the Caucasians [32]. Ethnic groups in the UK such as the South Asian population, have especially high rates of hypovitaminosis D [33-35]. It is therefore important to examine the effectiveness of vitamin D supplementation on levels of glycaemia among people of different ethnic groups in the same study, to add to the literature on this topic [16,18,19,36].

We aim to address these unresolved issues, especially concerning the nature of the association between vitamin D and metabolic parameters among people at risk of diabetes. We particularly wanted to include men and women of different ethnic groups, evaluate effects of an adequate dose of supplementation, and test the relative efficacy of vitamin D_2_ and D_3_ versus placebo among those at elevated risk of diabetes. The results obtained should provide high quality scientific evidence to improve understanding, and will also help to inform the conduct of larger trials with disease end points such as diabetes and cardiovascular disease.

### Objectives

The primary objective of this trial is to determine whether oral supplementation with vitamin D_2_ or vitamin D_3_ can lead to reduction in glycaemia and an improvement in related metabolic abnormalities in people at risk of developing diabetes.

The secondary objectives of this trial are (i) to examine the feasibility and acceptability of vitamin D supplementation to inform the design of a future RCT with diabetes and/or cardiovascular endpoints, and (ii) to compare the efficacy of vitamin D_2_ and vitamin D_3_.

## Methods/design

We designed a double-blind, placebo-controlled randomised clinical trial amongst people at risk of developing T2D, across two sites - East London and Cambridge, UK. We are randomly allocating 342 participants to one of three groups, to receive a monthly dose for four months, of 100,000 IU (equivalent to 2.5 mg) of either cholecalciferol (vitamin D_3_) or ergocalciferol (vitamin D_2_) or a monthly dose of placebo (miglyol oil). Each participant is followed-up for a total of 4 months from their first visit. The inclusion and exclusion criteria of the trial are as follows.

### Inclusion criteria

Men and women aged 30–75 years, from any ethnic group, who can provide informed consent for participation in the trial and are at a high risk of developing type 2 diabetes are included.

Risk of developing diabetes is defined by the following criteria:

A. Non-diabetic hyperglycaemia; either impaired glucose tolerance (IGT) or impaired fasting glucose (IFG) as defined by current World Health Organisation (WHO) criteria [37], or HbA_1c_ between 5.5% and 6.49% (equivalent to 37 to 47 mmol/mol), where this information is available in medical records (London), or in the records of studies in which the participants have consented to being re-approached to consider participating in future studies (Cambridge), or,

B. Cambridge Risk Score (CRS) [38-41] cut offs that indicate increased risk for diabetes. The CRS cut-offs are 0.236 for the Black/Caribbean population, 0.127 for South Asians and 0.199 for Caucasians [39]. For other groups the cut-off for Caucasians is used. This approach is used at the London site.

### Exclusion criteria

Participants are excluded if they have a known history of diabetes or have used oral hypoglycaemic agents, have random blood glucose during initial screening >11 mmol/l, have known intolerance to vitamin D_2_ or D_3_ within the previous two months or are currently using vitamin D supplements, have a known history of hypercalcaemia (serum calcium >2.65 mmol/l) or point of care ionised calcium >1.3 mmol/l. They are also excluded if they have known stage 4 or worse chronic kidney disease (eGFR (estimated glomerular filtration rate) < 30 ml/min), a history of significant liver disease (AST (aspartate aminotransferase) >3 x upper limit of normal (ULN) or ALT (Alanine aminotransferase) >3 x upper limit of normal (ULN) or serum bilirubin > 2.5 x ULN), a known history of renal stones, hyperparathyroidism, active sarcoidosis, tuberculosis or malignancy (active defined as currently on treatment and/or medication for the above conditions), have taken cardiac glycosides or oral/ intramuscular/intravenous corticosteroids (excluding inhaled and topical corticosteroids) in the past one month. They are excluded if they have known current anaemia (haemoglobin <11 g/dL) or haemoglobinopathy such as sickle cell anaemia and beta or alpha thalassemia. Additionally, if they plan to travel out of the London or Cambridge area (depending on site of recruitment) within 8 weeks of enrolment such that it would disrupt monitoring of the participant, they are excluded. Among women, current breast feeding, pregnancy or planning a pregnancy are also considered exclusion criteria.

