### Safety

The vitamin D investigational medicinal products used in this trial have undergone safety and quality checks, and are prescribed by a registered medical practitioner in both study centres. We wanted to use an adequate dose of vitamin D and after careful consideration opted for a dose of 100,000 IU per month, in order to increase the likelihood of generating a significant difference in vitamin D status between the treatment and placebo groups. There have been several trials in which high doses of vitamin D were administered without any adverse events. In an Indian randomised controlled trial, supplementation in men with three doses of 120,000 IU of vitamin D at fortnightly intervals was not associated with any adverse events in general or specifically relating to hypercalcaemia [36]. In a Canadian trial, 4000 IU of vitamin D_3_ daily for 2–5 months in healthy adults did not result in any adverse effects [46]. Two clinical studies of 10,000 IU/day have demonstrated an elevation of serum 25(OH)D concentrations to the high end of normal concentrations without inducing toxicity in healthy volunteers [44,45]. The recent IOM (Institute of Medicine) aforementioned review revised the safe dose of vitamin D upwards from 2000 IU/day to 4000 IU/d, which the dose we are supplementing falls well within [21]. Side effects of vitamin D supplementation are rare and include gastrointestinal symptoms (such as nausea, constipation, or diarrhoea), hypercalcaemia, hypercalcuria and associated kidney stones. To minimise risk of hypercalcaemia and hypercalcuria amongst predisposed individuals, we exclude individuals with known sarcoidosis, malignancies and tuberculosis. As a safety precaution, three measures are recorded for all recruited participants at all trial visits: a point of care ionised calcium test, a laboratory serum corrected calcium test and a laboratory urinary calcium to creatinine ratio test. Trial participants who have high point of care ionised calcium (>1.3 mmol/L) or urine calcium:creatinine ratio (molar ratio >1) or serum corrected calcium > 2.65) are excluded from further doses of the IMP, but continue to be followed up. Additionally, provision has been made for the recording of adverse events or reactions.

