### Recruitment

#### London site

Electronic searches of lists of patients in GP practices in East London are done by the practice staff to identify suitable participants. The Cambridge Risk Score (CRS) [38-41] is used to identify participants who are at high risk for T2D. In addition, a previous record of the presence of impaired glucose tolerance, impaired fasting glucose or non-diabetic hyperglycaemia assessed by HbA_1c_ is used to identify potential eligible participants. Practice staff extract information from the medical records on the following variables which comprise the Cambridge Risk Score: age, sex, smoking status, family history of diabetes, body mass index and whether the patient is prescribed anti-hypertensive or steroid medication. In addition, they extract information on ethnicity. Once identified, and after applying exclusion criteria that can be accessed from medical records, potential participants receive a letter inviting them to participate in the trial, a reply slip, a patient information sheet and a flyer with contact information. Potential participants who reply expressing an interest are telephoned by a member of the study team to provide further information as required and to arrange an appointment to attend a research centre.

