### Cambridge site

In Cambridge, participants are recruited from the Fenland study, an on-going population-based observational study investigating the influence of lifestyle and genetic factors on the development of diabetes, obesity, and other metabolic disorders [47]. Residents of Cambridgeshire, in the east of England, born between 1950 and 1975 are potentially eligible to participate in the Fenland Study and are excluded by their general practitioner if they have been diagnosed with diabetes or a terminal illness with a prognosis of less than one year, have a psychotic illness, are pregnant or lactating, or if they are unable to walk unaided. Approximately 28% of those registered with participating general practices in the Cambridgeshire Primary Care Trust have enrolled in the Fenland Study (more than 8,000 participants). Fenland study participants are eligible for this trial if they had agreed to be contacted again to gauge interest in involvement in future studies and do not meet the trial exclusion criteria. Potential participants are mailed an invitation letter for the trial, an information sheet and a flyer with contact information. Those interested in taking part are asked to complete the response form and to return it in an enclosed freepost reply envelope. In the event of non-response, a second mailing is sent approximately four weeks after the first. Responders are excluded from the trial if they have been diagnosed with diabetes or are actively participating in another trial, or if any of the trial exclusion criteria apply. For eligible participants, telephone contact is made and any queries are addressed before setting an invitation date for the baseline visit. In Cambridge, HbA_1c_ is primarily used as the eligibility criterion for identifying increased risk of diabetes.

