### Trial procedures and follow-up

As shown in the Figure 1, each participant has a total of 4 visits to the trial centre and one telephone call at 3 months to discuss the appropriateness of taking the final of the four doses of IMP. The initial visit includes informed consent, assessment of eligibility, administration of questionnaires regarding physical activity, diet, sun exposure, functional status, health utility, and a brief pain inventory, randomisation and administration of the first dose of study IMP. Subsequent visits (and the telephone call) are at monthly intervals. Second and third visits are for safety assessment and observation of consumption of the next two doses of the study IMP, while the 4^th^ (last) dose of the IMP is taken at home prompted by a phone call from the trial staff, if prior safety checks are within normal limits. The final follow-up visit is at the end of 4 months, when questionnaires are repeated and a final set of blood samples are collected.

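### Active disease is defined by current treatment, so known, current but untreated sarcoidosis (and perhaps tuberculosis and malignancy) is not excluded by diagnosis, although the Safety section says known cases are

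*Protocol article*

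**What the plan says.** The Exclusion criteria list, among conditions of which a participant may have no known history, "active sarcoidosis, tuberculosis or malignancy (active defined as currently on treatment and/or medication for the above conditions". The Safety section describes the same safeguard and gives its purpose, without mentioning activity or treatment: "To minimise risk of hypercalcaemia and hypercalcuria amongst predisposed individuals, we exclude individuals with known sarcoidosis, malignancies and tuberculosis".

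Three other parts of the article bear on the point.

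- **Calcium at entry (Exclusion criteria).** People are excluded if they "have a known history of hypercalcaemia (serum calcium >2.65 mmol/l) or point of care ionised calcium >1.3 mmol/l". Renal stones and hyperparathyroidism are also listed.
- **Calcium during the trial (Safety).** Ionised calcium, serum corrected calcium and the urine calcium to creatinine ratio are recorded at all visits. Participants above threshold on any of them "are excluded from further doses of the IMP, but continue to be followed up".
- **Who applies the list (Recruitment).** London sends invitations "after applying exclusion criteria that can be accessed from medical records". Cambridge drops responders for several reasons, "or if any of the trial exclusion criteria apply". Its source cohort had already removed people with "a terminal illness with a prognosis of less than one year".

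**The concern.** The Safety section ties the raised calcium risk to having the disease. The exclusion criterion tests whether the disease is being treated. These are different things: a person who has been diagnosed and is waiting to start treatment, or is under observation only, has the condition but is not active as the article defines it. Because the word is defined expressly, a recruiter who follows the text has little room to apply a clinical sense of active instead.

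What is at stake is participant safety and an accurate description of the safeguard. People whom the article itself calls predisposed could be given high-dose vitamin D, while the Safety section implies that they are kept out. Two sites with different recruitment sources could also settle the ambiguity differently.

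**Working it through.** No figure in the article needs reproducing, so the check is a comparison of texts.

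**Step 1: how far does active reach?** The adjective stands directly before sarcoidosis, and the definition that follows refers to conditions in the plural.

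- Reading A: active governs all three conditions. The plural in the definition favours this.
- Reading B: active governs sarcoidosis alone, so any known history of tuberculosis or malignancy excludes.

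**Step 2: who is excluded by diagnosis under each rule?**

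| Known disease state | Exclusion criteria, reading A | Exclusion criteria, reading B | Safety section, read literally |
|---|---|---|---|
| Sarcoidosis, current, treated | excluded | excluded | excluded |
| Sarcoidosis, current, untreated | **not excluded** | **not excluded** | excluded |
| Tuberculosis or malignancy, current, treated | excluded | excluded | excluded |
| Tuberculosis or malignancy, current, untreated | **not excluded** | excluded | excluded |

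Untreated current sarcoidosis falls through on both readings (1 of 3 conditions under B). All 3 fall through under A. No other section excludes such a person on the diagnosis.

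**Step 3: do the other safeguards close the gap?**

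- *Entry calcium.* The ionised calcium limit of 1.3 mmol/l and a known history of hypercalcaemia remove anyone with raised blood calcium, whatever the cause. They do not remove a person with normal calcium. The entry list has no urine calcium criterion, although hypercalciuria is one of the two harms named in the Safety section.
- *Timing of the first dose.* Under Trial procedures and follow-up, "The initial visit includes informed consent, assessment of eligibility", and also randomisation and the first dose. A person with normal calcium and untreated disease can therefore receive 100,000 IU at that visit. The next scheduled check is one month later.
- *Stopping rule.* The thresholds on all three calcium measures prevent further doses. They do not act on the first.
- *Fourth dose.* It is taken at home after the telephone call at 3 months. Safety samples are taken only at the four visits, so the latest result available comes from the third visit, when the third dose is given.
- *Cambridge cohort.* The terminal-illness exclusion does not reach non-terminal untreated disease, and nothing equivalent is described for London.

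The gap that remains is a known, current, untreated case with ionised calcium at or below 1.3 mmol/l and no known history of hypercalcaemia or other exclusion.

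**The case against.** The strongest reply is that there is only one operative rule. The Exclusion criteria are the formal list, and both sites are told to apply it. The Safety sentence is narrative in a condensed article and may simply have dropped a qualifier. On that view the sites receive no conflicting instruction. This largely stands as an account of how the two wordings arose. It does not rescue the operative rule, which still turns on treatment status when the stated purpose turns on disease.

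A second reply is that treatment and medication are named separately, so treatment might cover anyone under clinical management. That is possible but strained: a person diagnosed and awaiting treatment is not currently on it.

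A third is that the feared harm is screened directly. Blood calcium is tested at entry, blood and urine calcium are measured at every visit, a registered medical practitioner prescribes the product and the general practitioner is told of enrolment. This stands and is why the point is minor. It does not reach the first dose.

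Stronger inferences are not supported by the article:

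- *All three conditions are certainly affected.* Only sarcoidosis is in the gap on both readings. Tuberculosis and malignancy depend on how far active reaches.
- *The literal Safety sentence is the right standard, so everyone who has ever had these diseases should be excluded.* Limiting the exclusion to active disease suggests that resolved disease was meant to stay eligible, which is reasonable.
- *Participants would be harmed, or calcium events would rise, by some amount.* The article gives no number of such people and no event rate from which to estimate one.

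**Conclusion.** The point holds as a minor safety correction. The treatment-based definition leaves known, current but untreated sarcoidosis eligible. On the likelier reading it does the same for tuberculosis and malignancy. The Safety section tells readers otherwise. Both wordings are in the text, so this is not detail left to a fuller document.

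Its size is 1 of 3 conditions on the narrow reading and 3 of 3 on the wider one. That counts conditions, not people or risk; the number affected is unknown. The primary analysis of HbA1c and the target of 342 are untouched.

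The conclusion assumes that sites follow the definition as printed and that treatment carries its ordinary meaning.

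**What to change.** In the Exclusion criteria, replace the definition of active with: current disease, whether treated, awaiting treatment or under observation, or currently on treatment for it. State that it applies to each of sarcoidosis, tuberculosis and malignancy, and that it is judged at the eligibility assessment from available records and the participant's history. Resolved or cured disease stays eligible. Reword the Safety sentence to give the same rule.

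Do not require documented proof of resolution. That would shut out people with old disease and incomplete records. It would also be hard to apply at Cambridge, where the article describes no medical-record review for trial entry.

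The cost is one phrase, one matching sentence and a question at the eligibility assessment. The downside is some extra screen failures. The article gives no figure for these; the assumption is that they would be few.
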